## Abstract

**Background:**

Besides its classical role in musculoskeletal diseases, vitamin D deficiency has recently been found to be associated with cardiometabolic risks such as hypertension, diabetes mellitus and hypercholesterolemia. Although Malaysia is a sunshine-abundant country, recent studies found that vitamin D deficiency prevalence was significantly high. However, few published studies that measured its effect on cardiometabolic risk factors were found in Malaysia. There are also limited clinical trials carried out globally that tried to establish the causality of vitamin D and cardiometabolic risks. Therefore, a double blind, parallel, randomized controlled trial on vitamin D and cardiometabolic risks is planned to be carried out.

The objective of this study is to investigate whether vitamin D supplements can reduce the cardiometabolic risk and improve the quality of life in urban premenopausal women with vitamin D deficiency.

**Methods/design:**

Three hundred and twenty premenopausal women working in a public university in Kuala Lumpur, Malaysia will be randomized to receive either vitamin D supplement (50,000 IU weekly for 8 weeks and 50,000 IU monthly for 10 months) or placebo for 12 months. At baseline, all participants are vitamin D deficient (≤ 20 ng/ml or 50 nmol/l). Both participants and researchers will be blinded. The serum vitamin D levels of all participants collected at various time points will only be analysed at the end of the trial. Outcome measures such as 25(OH) D3, HOMA-IR, blood pressure, full lipid profiles will be taken at baseline, 6 months and 12 months. Health related quality of life will be measured at baseline and 12 months. The placebo group will be given delayed treatment for six months after the trial.

**Discussion:**

This trial will be the first study investigating the effect of vitamin D supplements on both the cardiometabolic risk and quality of life among urban premenopausal women in Malaysia. Our findings will contribute to the growing body of knowledge in the role of vitamin D supplements in the primary prevention for cardiometabolic disease.

**Trial registration:**

ACTRN12612000452897

## Background

Vitamin D or also known as the “sunshine vitamin” is a fat-soluble vitamin that is associated with bone health. It is well recognized that vitamin D deficiency leads to rickets in children and osteomalacia and osteoporosis in adults
[1]. However, recent findings have recognized unknown roles of vitamin D such as in the renin production in the kidney
[2-4], insulin production in the pancreas
[5-7], production of cathelecidin in macrophages
[8,9] and growth and proliferation of both vascular smooth muscle cells and cardiomyocytes
[7]. With these brand new discoveries, vitamin D maybe be associated with diseases such as hypertension, diabetes mellitus, hyperlipidemia and cardiovascular diseases
[1,9-11].

A few observational studies have shown significant inverse correlation between blood pressure and renin-angiotensin activity
[2,12-15]. An observational study in Korea also found a strong inverse association of vitamin D and hypertension
[16].

Low serum vitamin D level has been proven to be inversely correlated with type 2 diabetes mellitus. It is known that normal insulin secretion in pancreatic ß-cells depends on vitamin D. A reduction in vitamin D level can result in an increase in insulin resistance and reduction in insulin secretion
[2,6,9]. The prevalence of type 2 diabetes mellitus among South Asian origin women living in New Zealand with lower serum Vitamin D is three times higher than the New Zealand national incidence for diabetes
[16].

Other mechanisms by which vitamin D may protect against cardiovascular disease is through decreased levels of triglycerides and low-density lipoprotein cholesterol. This is possible as vitamin D increases the lipoprotein lipase activity in adipocytes
[17]. In addition, improving vitamin D levels will reduce the risk of developing type 2 diabetes mellitus and this will further reduce the lipoprotein disorders thus reducing the risk of cardiovascular diseases
[18].

With these new discoveries, vitamin D deficiency could be considered as a new modifiable risk factor for cardiometabolic disease; however, this needs more persuasive evidence. Many observational studies indicate the association between vitamin D and cardiometabolic risks
[10,17,19]. However, very limited trials are available to provide stronger evidence on the relationship between vitamin D and cardiometabolic risks. To date, only few clinical trials investigate cardiometabolic risks as its primary outcomes
[14,16,20-23]. The results of these clinical trials are also often inconsistent in the effects of vitamin D supplementation on cardiometabolic risks, especially among the small trials
[14,16,17,21,24-26]. Therefore, there is a need to determine whether treating vitamin D deficiency using vitamin D supplements could contribute to the prevention of cardiometabolic diseases.

The ultra-violet B (UVB) ray from the sun is the major and inexpensive source of vitamin D compare to other natural sources such as food, which contains a very small amount of vitamin D. Nevertheless; the prevalence of vitamin D deficiency is still high globally. In the United States, the prevalence of vitamin D deficiency was 25% to 57% as reported in the Third National Health and Nutrition Examination Survey (NHANES III)
[27], whereas the prevalence of vitamin D deficiency was 28% in the Framingham Offspring Cohort study
[19] and 47.8% in a study in Amsterdam
[28]. This prevalence will remain elevated during the winter seasons, especially among the elderly and homebound geriatric patients
[29-31]. Although vitamin D deficiency is common among people living in higher latitude countries, surprisingly high prevalence of vitamin D deficiency is also found in countries nearer to the equator which supposed to get sufficient sunlight all year round. Countries like Iran reported 61% of vitamin D deficiency
[10], 64.6% in Bangkok, Thailand
[32] and 66.3% in India
[33]. These high rates of vitamin D deficiency and its association with cardiometabolic diseases suggesting an ever expanding importance of vitamin D roles in our health and well-being.

Malaysia is located in latitude 2° 30’ N and is blessed with sufficient sunshine all year round necessary for cutaneous synthesis of vitamin D. Khor et al.
[34] however, reported that almost 35.3% of primary school children in Kuala Lumpur were vitamin D deficient, while approximately 70% of Malay adults in Kuala Lumpur were found to have vitamin D deficiency
[35]. In addition, both studies found an inverse association between vitamin D status and obesity. These findings raise concerns as the prevalence of obesity in Malaysia is also on the rise
[36]. Metabolic syndrome was found to be associated with vitamin D deficiency among Malay adults
[35]. Therefore, there is a need for conclusive evidence from randomized controlled trials (RCT) to evaluate the roles of vitamin D in the primary prevention of cardiometabolic risks.

Therefore, we proposed to start a RCT with the following objectives:

i. To investigate whether vitamin D supplements can improve cardiometabolic risk factors such as blood pressure (BP), homeostasis model assessment insulin resistant (HOMA-IR), triglycerides (TG) and high-density lipoprotein cholesterol (HDL).

ii. To investigate whether vitamin D supplements can improve the vitamin D status of urban premenopausal women who are vitamin D deficient.

iii. To investigate whether vitamin D supplements can improve the health-related quality of life.

## Methods/design

### Study design

This is a double-blind, randomized placebo-control, parallel trial in which the participants will be randomized into 1:1 ratio.

### Setting

This study will be conducted at a public university in Kuala Lumpur, Malaysia. Kuala Lumpur is located near the equator at latitude 03° 09’N.

### Participants

All premenopausal women working in the public university will be invited for screening for their eligibility.

### Inclusion/exclusion criteria

All premenopausal women aged 30 years old and above with vitamin D deficiency; serum 25(OH)D level ≤ 20 ng/ml (or ≤ 50 nmol/l), will be invited to participate in this study. Premenopausal women are included as they will be at a lower risk for osteoporosis than post-menopausal women if they are vitamin D deficient.

Those with an abnormal level of serum parathyroid hormone (PTH) (>55 pg/ml) and serum calcium (> 10.4 mg/dl), known to have illnesses such as granuloma forming disorder (e.g. Tuberculosis), lymphoma, sarcoidosis or any type of cancers will be excluded. Women taking vitamin D supplements containing > 1000 IU/day or any forms of calcitriol (1,25(OH)_2_D_3_) will be excluded. Pregnant women or participants who were found to be pregnant during the study will also be excluded from the study.

### Sample size estimation

According to the study by Zittermann et al.
[25], participants from the intervention arm with vitamin D supplementation was found to achieve a reduction in triglycerides of 0.19 ± 0.54 mmol/L and a change in mean for LDL-cholesterol of 0.19+1.03 mmol/L. Sample size calculation was conducted using OpenEpi version 2.3.1 Software. With a power of 80% and a two-sided 5% significant level, a minimum of 88 participants per arm is required using the results on triglycerides, while 146 participants is required with the results on LDL-cholesterol. In order to achieve adequate power, additions of 10% are added to 146 to account for possible attrition. Ultimately, the desired sample size for this study is 160 participants for each arm with a total of 320.

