### Data handling and statistical analysis

We will use Microsoft Access to maintain the demographic data. To record the progress of each participant throughout the trial period, we will use a check box to allow for easy access and follow-up purposes. Raw data obtain from the questionnaire and blood results will be entered into SPSS software version 16.0 (SPSS Inc., 2009, Chicago, Illinois). The data will be cleaned and checked for coding errors. Preferably, data will be double-entered to check for duplication and outliers before commencement of statistical analysis.

For baseline characteristics, descriptive statistics will be used. Categorical data will be described using count, percentages and 95% confidence intervals when applicable. Exact test on proportions will be used to compare categorical variables since this is a comparative trial data. All numerical data will be checked for normality. For normally distributed data, mean with standard deviation, independent t-test will be used and analyse using SPSS 16.0. However, if the data is found to be non-normally distributed or have un-equal variances, exact (permutation) tests will be used. Exact tests analyses will be undertaken using *StatXact*_*®*_ 9 (Cytel Inc.).

The primary analysis will be performed to explore intervention’s effects on HOMA-IR, LDL-cholesterol, TG, HDL and BP These analyses will be following the “intention-to-treat” principle in the comparison between the intervention and the placebo group at 6 months and 12 months. Additionally secondary analyses will be a comparison of change of the vitamin D status and health-related quality of life. Level of statistical significance is preset at p < 0.05.

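### The 80% power rests on changes of 0.19 mmol/L with no placebo figure, and the stated 88 and 146 per arm do not follow from those inputs for the active-versus-placebo comparison

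*Protocol article*

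**What the plan says.** Under Sample size estimation, the protocol article takes its planning figures from one published trial. For triglycerides, "participants from the intervention arm with vitamin D supplementation was found to achieve a reduction in triglycerides of 0.19 ± 0.54 mmol/L". For LDL it gives "a change in mean for LDL-cholesterol of 0.19+1.03 mmol/L", with no direction and without saying whether this is one arm's change or a difference between arms. The plus sign is read here as ±.

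The error rates and results follow: "With a power of 80% and a two-sided 5% significant level", then "a minimum of 88 participants per arm is required using the results on triglycerides", "while 146 participants is required with the results on LDL-cholesterol". The LDL figure sets the size of the trial: "additions of 10% are added to 146 to account for possible attrition", giving 160 per arm and 320 in all. OpenEpi is named as the software. The values entered in it are not listed.

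Under Data handling and statistical analysis, the primary analysis of HOMA-IR, LDL, triglycerides, HDL and blood pressure is by intention to treat, "in the comparison between the intervention and the placebo group at 6 months and 12 months". The independent t-test is used for normally distributed data.

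**The concern.** In a parallel placebo-controlled trial, power depends on the active change minus the placebo change and on the variability in both arms. The section prints neither the placebo change nor the difference. For triglycerides it says outright that the 0.19 belongs to the intervention arm. A change within one arm can include time trend and regression to the mean, which a placebo arm would share. It therefore cannot stand in for the between-arm effect without the placebo figure.

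The reader also cannot recover the missing figure by working back, because the printed inputs and the printed sample sizes disagree. What is at stake is how a null lipid result will be read. An article that claims 80% power next to an effect of 0.19 invites the conclusion that a between-arm effect of 0.19 has been adequately tested. For LDL, at the printed SD, it would not have been.

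**Working it through.** **Inputs** (all from Sample size estimation): triglycerides 0.19, SD 0.54; LDL 0.19, SD 1.03; two-sided 5%; 80% power; 1:1 allocation (Study design). The 146 is read as per arm, because it leads to 160 per arm. The ± figures are read as SDs of change.

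**1. Attempt to reproduce 88 and 146.** The two-sample formula is n per arm = 2 × (1.960 + 0.842)² × (SD/difference)², with (1.960 + 0.842)² ≈ 7.85.

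- Triglycerides: 2 × 7.85 × (0.54/0.19)² = 15.70 × 8.08 ≈ 127. Stated: 88.
- LDL: 2 × 7.85 × (1.03/0.19)² = 15.70 × 29.39 ≈ 462. Stated: 146.

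Other readings do not recover the stated numbers either:

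| Calculation with 0.19 | Triglycerides | LDL |
|---|---|---|
| Two-sample, two-sided | 127 | 462 |
| Two-sample, one-sided | 100 | 364 |
| Before-after in one arm, two-sided | 64 | 231 |
| Before-after in one arm, one-sided | 50 | 182 |
| Stated | 88 | 146 |

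**2. Could unequal SDs explain it?** With a difference of 0.19, the two arm variances must sum to n × 0.19²/7.85.

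- LDL: 146 × 0.0361/7.85 ≈ 0.67. One arm alone contributes 1.03² ≈ 1.06, so the other variance would have to be negative. A difference of 0.19 with one arm's SD at 1.03 cannot give 146.
- Triglycerides: 88 × 0.0361/7.85 ≈ 0.405; less 0.54² = 0.292 this leaves 0.113, a placebo SD of about 0.34. That is possible but not stated.

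**3. What 88 and 146 do correspond to.** With the printed SD in both arms, difference = SD × 2.802 × √(2/n).

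- Triglycerides: 0.54 × 2.802 × √(2/88) ≈ 0.228.
- LDL: 1.03 × 2.802 × √(2/146) ≈ 0.338.

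These exceed 0.19 by about 0.04 and 0.15. A placebo change of that size in the opposite direction would produce them. Alternatively, a difference of 0.19 would need common SDs of about 0.45 and 0.58.

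**4. Power if the between-arm difference is 0.19.** Power = Φ(difference/(SD × √(2/n)) − 1.96).

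- Triglycerides: about 65% at 88 per arm and 85% at 146.
- LDL: 0.19/(1.03 × √(2/146)) = 1.576, so Φ(−0.384) ≈ 35% at 146 per arm. At 160 it is Φ(1.650 − 1.960) ≈ 38%.

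**5. Dependence on the placebo change.** The article does not give this change, so the values below are assumptions, with a common SD in both arms.

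| Assumed placebo change relative to active | Difference | n per arm for 80% | Power at 146 per arm |
|---|---|---|---|
| Triglycerides, same direction by 0.05 | 0.14 | 234 | 60% |
| Triglycerides, none | 0.19 | 127 | 85% |
| Triglycerides, opposite by 0.04 | 0.23 | 87 | 95% |
| LDL, same direction by 0.05 | 0.14 | 850 | 21% |
| LDL, none | 0.19 | 462 | 35% |
| LDL, opposite by 0.15 | 0.34 | 145 | 81% |

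**6. Detectable differences at the planned size.** 160 less 10% is 144 completers per arm. At 80% power a two-sided t-test detects 0.179 mmol/L for triglycerides (SD 0.54) and 0.341 mmol/L for LDL (SD 1.03).

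**The case against.** A reader might infer that the sample size was calculated on the wrong contrast, with the active arm's own 0.19 entered as if it were the between-arm effect. The documents do not support that. The section reports a published result, names the software and gives n, but never says which difference was entered. Its own numbers speak against 0.19: steps 1 and 2 show that 0.19 with the printed SDs does not give 146 for LDL, and gives 88 for triglycerides only with an unstated placebo SD. The differences in step 3 are larger and could already be active minus placebo. That is also inference, and settling it would need the cited trial's placebo arm.

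Two further limits stand. The LDL shortfall to 35% appears before any placebo change is assumed, so it measures the mismatch between inputs and n and not the effect of an omitted placebo arm. For triglycerides, likewise, a placebo fall of 0.05 moves the requirement from 127 to 234. The step from 88 to 127 is the separate failure to reproduce.

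It may also be said that a journal article condenses a fuller protocol, so the placebo inputs may be recorded elsewhere. Their absence alone would not be a finding. But the article prints inputs, error rates and results together as a justification, and they do not agree. That is a fault in what is stated, and it remains whatever the fuller document contains.

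**Conclusion.** The point holds as a failure of justification. The printed inputs do not support 80% power for the active-versus-placebo comparison, and they do not generate 88 or 146. Taken as a between-arm difference, 0.19 requires about 127 and 462 per arm. LDL, the outcome that fixes the trial's size, then has about 35% power at 146 per arm and 38% at 160. For triglycerides the planned size remains adequate if the between-arm difference is 0.19.

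These figures assume a two-sample comparison of means, the printed SDs in both arms and no placebo change. It does not follow that the trial is underpowered for the difference its designers had in mind. If that was about 0.34 mmol/L for LDL, 146 per arm is right and only the text is deficient. The article does not show which case applies.

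**What to change.** In Sample size estimation, state the active-minus-placebo difference and the SD of change in each arm that were actually used for triglycerides and for LDL, with the direction of the LDL effect. Restate n and power for that contrast so that a reader can reproduce them.

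If those figures are not available, remove the 80% claim tied to 0.19 and keep the total at 320. Wording could be: with about 144 completers per arm (160 less 10%), the trial has 80% power at two-sided 5% to detect between-arm differences in change of about 0.18 mmol/L in triglycerides (SD 0.54) and 0.34 mmol/L in LDL (SD 1.03); a non-significant result will be interpreted against these differences using the confidence interval.

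The cost is a rewritten paragraph, with no extra participants. The downside is a less favourable stated power for LDL at a difference of 0.19.

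### The stated sample sizes of 88 (triglycerides) and 146 (LDL-cholesterol) per arm do not follow from the printed inputs, which give about 127 and 462 per arm

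*Protocol article*

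**What the plan says.** The Sample size estimation section of the Protocol article takes its inputs from one cited study: "a reduction in triglycerides of 0.19 ± 0.54 mmol/L and a change in mean for LDL-cholesterol of 0.19+1.03 mmol/L". It attributes them to the treated group of that study: "participants from the intervention arm with vitamin D supplementation was found to achieve a reduction in triglycerides". No change or SD for a comparator group is given, and no direction is given for the LDL change.

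The error rates are explicit: "With a power of 80% and a two-sided 5% significant level". The result is "a minimum of 88 participants per arm is required using the results on triglycerides, while 146 participants is required with the results on LDL-cholesterol". The larger figure is carried forward ("additions of 10% are added to 146 to account for possible attrition") to reach 160 per arm and 320 in total.

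The Study design section fixes equal allocation ("the participants will be randomized into 1:1 ratio"). The Data handling and statistical analysis section plans an independent t-test between the arms and lists both triglycerides and LDL-cholesterol in the primary analysis.

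**The concern.** The paragraph prints both the inputs and the outputs of its calculation, so the reader can check one against the other, and they disagree. Both outcomes share the effect 0.19 and differ only in SD, yet LDL, with nearly twice the SD, is said to need only 1.66 times as many participants.

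The LDL figure matters most because the total of 320 is built on it. A reader who accepts the paragraph would take a null LDL result as coming from a comparison with 80% power to detect 0.19 mmol/L. On the printed values the power would be little more than one third.

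There is also a mismatch of quantity. The change within a treated group is not the difference between treated and placebo groups, and the latter is what the planned test addresses.

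**Working it through.** **Inputs** (Sample size estimation, unless noted)
- Two-sided 5% and 80% power: z-values 1.960 and 0.842, so (1.960 + 0.842)² ≈ 7.849 (computed with unrounded z-values).
- Triglycerides: 0.19 mmol/L, SD 0.54. LDL: 0.19 mmol/L, SD 1.03 (the plus sign read as plus-minus).
- 1:1 allocation (Study design); independent t-test between arms (Data handling and statistical analysis).

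**Step 1. Try to reproduce 88 and 146.** For two means with a common SD, n per arm = 2 × 7.849 × SD² / difference².
- Triglycerides: 2 × 7.849 × 0.2916 / 0.0361 = 126.8, so 127 (128 with the t distribution). Stated: 88.
- LDL: 2 × 7.849 × 1.0609 / 0.0361 = 461.3, so 462 (463 with the t distribution). Stated: 146.

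**Step 2. Try other formulas.** None returns 88 or 146.

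| Variant | Triglycerides | LDL |
|---|---|---|
| Two-sample, two-sided, 80% | 127 | 462 |
| Two-sample, one-sided, 80% | 100 | 364 |
| Two-sample, two-sided, 90% | 170 | 618 |
| One-sample or paired, two-sided, 80% | 64 | 231 |
| One-sample or paired, one-sided, 80% | 50 | 182 |
| Two-sample, inputs moved by ±0.005 for rounding | 119-137 | 434-492 |
| Stated | 88 | 146 |

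**Step 3. Check the ratio.** Any formula proportional to SD²/difference² with a shared difference must give LDL/triglycerides = (1.03/0.54)² = 3.64, whatever the alpha, power or number of sides. The stated ratio is 146/88 = 1.66. One such formula cannot yield both figures from the printed inputs.

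**Step 4. Allow different SDs in the two arms, difference fixed at 0.19.** Then n = 7.849 × (SD₁² + SD₂²) / 0.0361.
- LDL: 146 per arm allows a summed variance of 146 × 0.0361 / 7.849 = 0.67. The printed SD alone contributes 1.06, so the comparator variance would have to be negative. With a comparator SD of zero, n = 7.849 × 1.0609 / 0.0361 = 230.7, so 231.
- Triglycerides: 88 per arm allows 88 × 0.0361 / 7.849 = 0.405, leaving 0.405 − 0.292 = 0.113, a comparator SD of about 0.34. That is possible, but it is not printed.

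**Step 5. What 88 and 146 would imply at the printed SDs.** Difference = 2.802 × SD × √(2/n).
- Triglycerides: 2.802 × 0.54 × √(2/88) = 0.228 mmol/L.
- LDL: 2.802 × 1.03 × √(2/146) = 0.338 mmol/L.

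**Step 6. Power at the planned size if 0.19 is the between-arm difference and the printed SDs are common to both arms.** Power ≈ Φ(difference / (SD × √(2/n)) − 1.960). Completers after 10% loss: 160 × 0.9 = 144.

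| n per arm | Triglycerides | LDL |
|---|---|---|
| 144 | Φ(2.986 − 1.960) = 85% | Φ(1.565 − 1.960) = 35% |
| 160 | 88% | 38% |

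The noncentral t gives 84.5% and 34.5% at 144, and 88.1% and 37.7% at 160. The LDL difference detectable with 80% power at 144 per arm is 2.802 × 1.03 × √(2/144) = 0.34 mmol/L, about 1.8 times 0.19.

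**The case against.** The strongest reply is that 0.19 was never claimed to be the between-arm difference. The article assigns it to the intervention arm, so the authors may have entered comparator-arm changes that they did not print. Differences of about 0.23 and 0.34 mmol/L at the printed SDs return 88 and 146. A smaller comparator SD lowers what is needed: with 0.7, an assumed value, √(7.849 × (1.0609 + 0.49) / 146) = 0.289 mmol/L suffices for LDL. Since the LDL change has no stated direction, an opposite change in the comparator group is not excluded.

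This stands, and it limits the conclusion. A reader might infer that the software calculation was wrong, or that the trial simply has 34-38% power for LDL. The document supports neither as a plain fact, because the comparator values are not shown. It supports the narrower statement that the printed inputs do not give the printed outputs.

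The reply does not remove the point. If other values were used, the paragraph omits what set the trial's size and prints values that give a different answer. Nor is this detail that an article would leave to a fuller document, because the article chose to print both ends of the calculation.

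Two further replies narrow the consequence. Triglycerides are adequately covered at 160 per arm on the printed values. LDL is one of several outcomes in the primary analysis and is absent from the first listed objective, although it does determine the 320. A baseline-adjusted analysis would not close the gap: none is planned, and if 1.03 were a cross-sectional SD, a correlation as high as 0.8 would still leave 462 × (1 − 0.64) ≈ 166 per arm.

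The way the 10% is added is not part of this point: 144 or 146 completers per arm makes no material difference.

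**Conclusion.** The concern holds as a failure to reproduce. From the printed values, a two-sample comparison needs about 127 per arm for triglycerides (stated 88) and about 462 for LDL (stated 146). With the difference at 0.19, LDL cannot fall below 231 per arm whatever the comparator SD. This rests only on the article's own figures.

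The power statement is conditional. If 0.19 is the between-arm difference and 1.03 the common SD, LDL power is about 34% with 144 completers per arm and 38% with 160. It should not be quoted without that condition.

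The total of 320 is not thereby shown to be unsuitable. If 0.19 and 0.54 apply between arms, it supports triglycerides. What is unsupported as written is its derivation through LDL.

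**What to change.** Keep 320 and correct the Sample size estimation paragraph, in this order.

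1. Print the between-arm differences, and the SDs for both arms, that produce 88 and 146, so that both figures can be reproduced.
2. If no such inputs exist, withdraw the 80% claim for LDL. State instead that 144 evaluable participants per arm give 80% power for an LDL difference of about 0.34 mmol/L at SD 1.03, and about 34% power for 0.19.
3. In that case, justify 320 on triglycerides, declaring as an assumption (not as a result of the cited study) that the between-arm difference is 0.19 mmol/L with a common SD of 0.54. That needs 127 evaluable per arm, or 127/0.9 ≈ 142 with 10% loss. At 144 evaluable per arm the power is about 84-85%.

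The cost is rewording one paragraph, with no extra participants. The downside is that, if step 2 applies, the stated LDL power becomes less favourable.
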